## Abstract

**Background::**

Postoperative gastrointestinal dysfunction (PGD) is a common complication of patients who have undergone surgery. The clinical manifestations cause great discomfort to postoperative patients and can severely affect postoperative recovery. However, although various pharmacologic agents have been explored for several years, success has been limited. Because some commonly used drugs have caused adverse reactions and because abdominal surgery patients generally cannot consume food or medication during the perioperative period, we were prompted to try an external Chinese medicine treatment method. Yikou-Sizi powder hot compress is an efficient therapy in our hospital, but there is a lack of rigorous studies to certify the safety and effectiveness of its external use to improve gastrointestinal motility. This study aimed to introduce the clinical trial design and test the ability of Yikou-Sizi powder hot compress treatment to accelerate gastrointestinal functional recovery after abdominal surgery.

**Methods::**

This study is a randomized controlled clinical trial. The participants will undergo laparoscopic colorectal cancer surgery and laparoscopic total hysterectomy. The primary outcome measure will be the gastrointestinal functional evaluation index, including the time to first passage of flatus, first defecation, first normal bowel sounds, and first consumption of liquid/semigeneral diet foods. According to good clinical practice (GCP), we will evaluate the clinical efficacy and safety of Yikou-Sizi powder hot compress and objectively study the acting mechanism of ghrelin. This pilot trial will be a standard, scientific, and clinical study designed to evaluate the effect of Yikou-Sizi powder hot compress for the recovery of gastrointestinal function after surgery and determine its overall safety.

**Discussion::**

This is the first study to describe the use of Yikou-Sizi powder hot compress to accelerate the recovery of gastrointestinal function after abdominal surgery. The study is designed as a randomized, controlled, clinical, large sample size and pilot trial. Evaluation will consist of combining the primary outcome measures with secondary outcome measures to ensure the objectivity and scientific validity of the study. Due to the observational design and the limited follow-up period, it is not possible to evaluate to what extent the connection between the observed improvement and the interventions represents a causal relationship. Efficient comparison between groups will be analyzed by chi-square test.

## Introduction

1

Postoperative gastrointestinal dysfunction (PGD) is a common postoperative complication of patients undergoing surgery.^[1–8]^ PGD is caused by surgical trauma, anesthesia, electrolyte disturbance, abdominal cavity inflammation, residual hemorrhage, or drainage tube mechanical stimulation.^[8–10]^ It is characterized by a series of symptoms such as nausea, vomiting, flatulence, defecation difficulty, abdominal distension, and abdominal pain, which are regarded as inevitable reactions after anesthesia and surgery.^[11]^ One of the worst complications is delayed resumption of gastrointestinal function, known as postoperative ileus (POI).^[12]^ This can prolong hospital stays, raise healthcare costs, and increase morbidity and mortality.^[9,13,14]^ POI usually resolves within approximately 3 days, although it can last longer in some cases as a condition termed postoperative paralytic ileus.^[15,16]^ Postoperative use of opioid-based analgesics can increase the incidence of POI.^[17,18]^ The treatment for the recovery of gastrointestinal function mainly focuses on rehydration, oxygen supply, electrolytes, acid–base imbalance, infection prevention, spasticity and pain relief, gastrointestinal decompression, prokinetic drug usage, and related hormonal intervention.^[19]^

Modern medicine attaches great importance to the rapid recovery of gastrointestinal function during the perioperative period, but it lacks active interventional measures. Various pharmacologic agents have been explored for several years, although success has been limited.^[20–28]^ The drugs that have been used as medical treatment for POI are commonly used prokinetic agents such as metoclopramide, domperidone, cisapride, and alvimopan. Domperidone and cisapride can cause adverse reactions that affect the cardiac system,^[29]^ and extrapyramidal reactions exist with metoclopramide use,^[30]^ limiting its clinical application. Its cardiovascular events have brought great risk when used by POI patients.^[31]^ Alvimopan opioid receptor antagonists have recently been developed in the United States for POI, and have been introduced in China, and mainly used in cases of colon failure and to improve gastrointestinal transit function after surgery and decrease postoperative inflammation caused by an excess of nitric oxide that is released after muscular layer infiltration.^[2,32,33]^ Therefore, when the local inflammatory response causes more intense symptoms of POI, alvimopan may no longer be an effective means to promote the recovery of POI.^[33,34]^

It has been proven that Chinese herbal medicines promote the recovery of gastrointestinal function. We have conducted many studies regarding gastrointestinal motility in recent years,^[35–37]^ and there are also many other researchers that have proven that Chinese herbal medicines can promote gastrointestinal functional recovery.^[38–41]^ Although herbal medicine shows some benefit for gastrointestinal motility, abdominal surgery patients generally cannot consume anything by mouth during the perioperative period.

Compared with drugs for internal treatment, the Chinese medicine external treatment method is easy to use, consists of simple materials, causes less adverse reactions, acts quickly, confers a good curative effect that is distinct, results in high patient compliance, and is highly effective. Therefore, Chinese medicine external treatment to promote the recovery of gastrointestinal function after surgery gradually has become a focus in the study of clinical medicine. Hence, rigorous studies are needed to certify the safety and effectiveness of external use of Chinese herbal medicine to improve gastrointestinal motility. Yikou-Sizi powder hot compress is an efficient therapy at our hospital (The Second Affiliated Hospital of Guangzhou University of Chinese Medicine). We consider that anesthesia and surgery lead to POI, which is known as Qi deficiency and Qi stagnation in Chinese medicine syndromes. Yikou-Sizi powder consists of: Fructus Tsaoko (Cao Guo; red cardamom fruit [*Amomum tsaoko*]), Semen Alpiniae Katsumadai (Cao Dou Kou; galangal seeds [*Alpinia katsumadai*]), Fructus Evodiae (Wu Zhu Yu; evodia fruit [*Evodia rutaecarpa*]), and Fructus Alpiniae Oxyphyllae (Yi Zhi Ren; black cardamom fruit [*Alpinia oxyphylla*]). They are all aromatic herbs to enliven and invigorate the spleen and resolve dampness.^[42]^ Furthermore, the 4 drugs (*A tsaoko*,^[43–46]^*A katsumadai*,^[47–55]^*E rutaecarpa*,^[56,57]^ and *A oxyphylla*^[58–60]^) have been studies that have anti-inflammatory, antioxidant activity, neuroprotective, or gastric protective activities. *E rutaecarpa* is effective in the treatment of bowel disorders^[61]^ and evodiamine is the major bioactive compound of *E rutaecarpa* have been shown to increase rat normal jejunal contractility.^[56]^ Both in vitro and in vivo permeation studies showed that *A oxyphylla* essential oils could effectively promote drug absorption across and/or into the skin.^[62]^ Of course, the action of the above mentioned drugs have a positive role to promote gastrointestinal functional recovery.

## Materials and methods

2

### Study design

2.1

This study is designed as a randomized, controlled, clinical, pilot trial. We will select patients who underwent laparoscopic colorectal cancer surgery and laparoscopic total hysterectomy between March, 2015 and June, 2019 at Guangdong Provincial Hospital of Chinese Medicine. The patients will be randomly assigned to the Yikou-Sizi powder hot compress group; or the conventional therapy group on the basis of numbers randomly generated using the website (http://www.gztcmgcp.com/sjxt/login.asp). We will evaluate the efficacy and safety of the Yikou-Sizi powder hot compress for patients who have undergone abdominal surgery by comparing the indexes in different groups, such as the time to first passage of flatus, time to first defecation, time to first normal bowel sounds, and time to the initiation of a liquid/semigeneral diet. The study protocol will be certified by the Institutional Review Board (IRB) of The Second Affiliated Hospital of Guangzhou University of Chinese Medicine (Guangdong Provincial Hospital of Chinese Medicine), and registered at the Chinese Clinical Trial Registry (http://www.chictr.org.cn/, ChiCTR-IOR-14005744).

The inclusion criteria, exclusion criteria, and elimination criteria which will be followed to ensure the accuracy of the results are described in the following subsections.

### Inclusion criteria

2.2

The inclusion criteria are as follows:

1)Underwent laparoscopic colorectal cancer surgery and laparoscopic total hysterectomy2)Age from 40 to 75 years old3)Anesthesia time was within 1.5 to 4.5 hours4)Duration of surgery was 1 to 4 hours5)The TCM syndrome was identified as Qi stagnation syndrome6)Willing to sign an informed consent document

### Exclusion criteria

2.3

The exclusion criteria are as follows:

1)Patients with malignant tumor(s) who required extended radical surgery2)Advanced malignant tumor with cachexia/extremely weak patient3)With cardiovascular, liver, kidney, brain, lung, and/or other serious diseases4)With mental disease5)Poor control of hypertension, diabetes6)Pregnant or breastfeeding women7)Severe malnutrition, serum albumin <21 g/L, prealbumin <0.1 g/L8)With allergies to the intervention9)Blood loss of more than 400 mL during surgery10)Reabdominal surgery and severe intestinal adhesion

### Study withdrawal and stopping medication

2.4

1)The condition worsens and cannot be controlled in 3 days2)Does not meet the inclusion criteria, but was included by mistake3)Refuses to continue the treatment, regardless of the reason4)Experiences serious complications, infection, or requires a second operation during the treatment5)Occurrence of other complications because of the interventions, including severe allergy or serious adverse events

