### Intervention

2.6

The Yikou-Sizi powder will be produced by Guangdong province Engineering Technology Research Institute of TCM, and they hold a Good Manufacturing Practice certificate.

After surgery, the groups will individually receive Yikou-Sizi powder hot compress and conventional therapy or only conventional therapy twice daily at 9:00 and 16:00 hours after surgery until the time to defecation. Conventional therapy will only include antibiotics and liquid support.

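### The protocol does not separate stopping treatment from leaving the study, so outcome-related withdrawals can bias the recovery-time comparison

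*Protocol article*

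**What the plan says.** Section 2.4 of the protocol article covers both leaving the study and stopping medication, and does not say which ground leads to which. It lists five grounds:

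1. "The condition worsens and cannot be controlled in 3 days"
2. "Does not meet the inclusion criteria, but was included by mistake"
3. "Refuses to continue the treatment, regardless of the reason"
4. "Experiences serious complications, infection, or requires a second operation during the treatment"
5. "Occurrence of other complications because of the interventions, including severe allergy or serious adverse events"

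Section 2.1 announces three sets of rules (inclusion, exclusion and elimination) to be described in the subsections that follow. It gives their purpose in the words "elimination criteria which will be followed to ensure the accuracy of the results". Sections 2.2 and 2.3 hold the inclusion and exclusion criteria, so the elimination criteria can only be section 2.4.

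Under section 2.6 the arms receive "Yikou-Sizi powder hot compress and conventional therapy or only conventional therapy". No sham compress is described. Section 2.8 blinds observers and statisticians. Section 2.9 makes times to first flatus, defecation, bowel sounds and diet the primary endpoints. Section 2.5 records bowel sounds until discharge, without addressing patients who have been withdrawn. Section 2.11 allows for 15% dropout.

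**The concern.** Four of the five grounds are events after randomisation that either bear on gut recovery or follow from the treatment given. A patient with a serious complication or a second operation is likely to have late flatus, late defecation and late diet. The Introduction notes that "POI usually resolves within approximately 3 days, although it can last longer in some cases", so patients whose condition is still uncontrolled after 3 days plausibly include some in the late tail of the recovery times that the trial sets out to shorten.

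If such patients leave the study, the late tail is thinned. The comparison suffers when the thinning differs by arm, and there are two ways it can:

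- **Reasons that exist in one arm only.** A control patient has no compress to refuse or react to.
- **A real effect.** If the compress works, fewer compress patients recover slowly, so identical rules remove more control patients than compress patients.

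A statistical analysis plan can define the analysis set, but it cannot recover recovery times that were never recorded because the patient had left the study.

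**Working it through.** **Inputs (section 2.11).** Time to first flatus: group 1 mean 75.47 h, SD 39.44 h; group 2 mean 64.29 h, SD 24.96 h. Planned difference: 75.47 − 64.29 = 11.18 h. Group 1, the slower, is taken as control. Dropout is 15%: 77/0.85 = 90.6, stated as 90. The article gives no loss by arm or by reason, so every split below is an assumption.

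**Step 1: the tail.** Assume a lognormal shape with the group 1 mean and SD.

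- σ² = ln(1 + (39.44/75.47)²) = 0.2415, so σ = 0.4914; μ = ln 75.47 − 0.2415/2 = 4.2030.
- P(T > 72 h) = 1 − Φ((ln 72 − 4.2030)/0.4914) = 1 − Φ(0.150) = 0.44. A gamma shape gives 0.47.
- Mean of those above 72 h = 75.47 × [1 − Φ(0.150 − 0.491)]/0.4404 = 108.6 h.

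**Step 2: shift in one arm.** If a fraction f of the arm is lost, at random from patients above 72 h, the arm mean falls by

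shift(f) = f × (108.58 − 75.47)/(1 − f) = 33.11 × f/(1 − f).

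| f | shift |
|---|---|
| 10% | 3.68 h |
| 12.5% | 4.73 h |
| 15% | 5.84 h |
| 17.5% | 7.02 h |
| 20% | 8.28 h |

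**Step 3: bias with no true effect** (both arms at 75.47 h, SD 39.44 h).

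| Loss in the two arms | Bias | Share of 11.18 h |
|---|---|---|
| equal | 0 h | 0% |
| 12.5% and 17.5% | 7.02 − 4.73 = 2.3 h | 21% |
| 10% and 20% | 8.28 − 3.68 = 4.6 h | 41% |
| 15% and 0% | 5.8 h | 52% |

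The first two unequal splits average the planned 15%. The last is extreme: it puts all loss in one arm and removes 0.15/0.44 = 34% of that arm's patients above 72 h. The gamma shape gives the same results to within 0.1 h. The sign follows the arm that loses more: extra loss from the compress arm favours the compress, and extra loss from control works against it.

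**Step 4: identical rules with a real effect.** Let group 2 be lognormal with mean 64.29 h and SD 24.96 h. Then P(T > 72 h) = 0.312, with tail mean 93.5 h. Remove 20% of the patients above 72 h in each arm.

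- Control loses 0.20 × 0.440 = 8.8%; its mean becomes (75.47 − 0.0881 × 108.58)/0.9119 = 72.3 h.
- Compress loses 0.20 × 0.312 = 6.2%; its mean becomes (64.29 − 0.0624 × 93.54)/0.9376 = 62.3 h.
- The difference shrinks from 11.2 h to about 9.9 h.

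**The case against.** The strongest reply is that the article nowhere says that withdrawn patients' data are deleted or left out of the primary analysis. The analysis set is commonly left to a full protocol or analysis plan, neither of which is shown, and section 2.5 exempts nobody from bowel-sound recording up to discharge. This stands as a limit. A reader might infer that the rule certainly removes poor outcomes unequally and biases the result, but the text supports only a risk. It does not dispose of the point, because the text that creates the risk is present: one list for withdrawal and stopping, presented as a safeguard of the results.

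Several stronger readings also fail:

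- Grounds 1 and 4 are worded alike for both arms.
- Ground 5 is not confined to the compress arm. It speaks of interventions in the plural, and both arms receive antibiotics. Only compress-specific reactions are one-armed, and known allergy to the intervention is already an exclusion criterion.
- Ground 1 is not the same as flatus after 72 h. It needs worsening that is not controlled, so a slow but uneventful recovery does not meet it. The 72 h cut above is a stand-in.
- Flatus or bowel sounds may be recorded before a patient is withdrawn.
- The trial is not wholly unblinded, since observers and statisticians are to be blinded. Patients evidently are not.

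**Conclusion.** The concern holds as a risk built into the stated rules. Section 2.4 does not distinguish stopping treatment from leaving the study, section 2.1 ties such rules to the accuracy of the results, and most of the grounds are linked to the primary endpoints or to treatment. Followed as written, they can remove slow recoverers, and compress-specific refusal or reaction can make the removal unequal.

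The direction is not fixed and the size cannot be derived from the document. The illustrative range is 0 to 5.8 h against a planned 11.18 h, with 2.3 to 4.6 h for the unequal splits averaging 15%. It rests on a lognormal shape, losses only from patients above 72 h, actual exclusion of those patients, and assumed splits by arm. Equal loss with no true effect gives no bias.

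**What to change.** - Leave the treatment-stopping grounds as they are, and state that stopping treatment is not leaving the study.
- Continue recording all primary endpoints to the event or discharge after treatment stops. State how each time is counted after a second operation.
- Include every randomised patient in the assigned arm in the primary analysis, including those enrolled by mistake. Use a per-protocol set only as a sensitivity analysis.
- End follow-up early only when consent is withdrawn.
- Where an event has not been seen by discharge or withdrawal of consent, use a method for censored times, such as a log-rank test or Cox model stratified by surgery type. The ANOVA and rank-sum test named in section 2.12 do not handle general censoring. Report censoring by arm and reason, since these methods assume it is unrelated to recovery.

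The cost is protocol and CRF wording, a modest change of analysis, and slight dilution from patients who stop early. Extra data collection is small, because these are inpatients already observed daily.

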### Trial procedure

2.5

The entire trial includes a preoperative assessment, an intervention phase (generally 7 days), and a 3-month follow-up phase. The included subjects will be randomized to the Yikou-Sizi powder hot compress group or the conventional therapy group through a stratified randomization system, and acquire a random number (corresponding to the Yikou-Sizi powder hot compress and conventional therapy group or conventional therapy group) in this phase. The participants will be instructed to apply a Yikou-Sizi powder hot compress twice every day at 9:00 and 16:00 hours starting after the surgery (the day of surgery was excluded) until the time to defecation. The bowel sounds of the included subjects will be evaluated at least three times per day (1:00–9:00, 9:00–17:00, and 17:00–1:00) after surgery and were recorded in the case report form (CRF) until the time of patient release from the hospital. Patients will be called on the 14th day and the 120th day to inquire about and monitor any adverse events (Fig. 1).

**Figure 1 F1:**
[figure not shown]
Study flowchart. The entire trial includes a preoperative assessment, an intervention phase (generally 7 days), and a 3-month follow-up phase.

### Intervention

2.6

The Yikou-Sizi powder will be produced by Guangdong province Engineering Technology Research Institute of TCM, and they hold a Good Manufacturing Practice certificate.

After surgery, the groups will individually receive Yikou-Sizi powder hot compress and conventional therapy or only conventional therapy twice daily at 9:00 and 16:00 hours after surgery until the time to defecation. Conventional therapy will only include antibiotics and liquid support.

### Randomization

2.7

Participants that had undergone laparoscopic colorectal cancer surgery (n = 220) and laparoscopic total hysterectomy (n = 220) will be randomly assigned to the Yikou-Sizi powder hot compress and conventional therapy group or conventional therapy group. The randomized number will be generated by the network (http://www.gztcmgcp.com/sjxt/login.asp) and saved by statistical professionals.

### Quality control

2.8

To ensure the quality of the research, this study protocol has undergone multiple modifications and revisions by relevant experienced surgeons, digestive disease specialists, research methodologists, and professional statisticians. To maintain data objectivity, we will ensure that the observers and statisticians were blinded. The entire routine will be monitored by independent quality inspectors. The CRF will be filled in accordance with the CRF instructions; in addition, no alterations will be allowed to be made to the original medical history and data record in the CRF, and any modifications will require a detailed explanation and the signature of the person who made the change. All the laboratory data will be thoroughly recorded, and we repeatedly will check for the existence of any significantly abnormal data and require that the physician notate the records with any necessary instructions regarding them. Because the patients will return any remaining medication, we will record this and be able to objectively determine patient compliance.

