### Endpoints

2.9

Primary endpoints are as follows: time to first flatus, time to first defecation, time to first bowel sounds, time to initiation of a liquid/semiliquid/general diet.

Secondary outcome measures are as follows: gastrointestinal symptoms, such as nausea, abdominal distention and pain, and vomiting; serum levels of hormones, including motilin, ghrelin, bradykinin, and corticotrophin-releasing hormone (CRH); and electrogastrogram.

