### Data collection and statistical analysis methods

2.12

The data will be collected and recorded in the CRF forms from participants via face-to-face and telephone interviews daily. The Epidata 3.1 Statistical Package was used for data entry. Two people will perform the data entry independently, and they will be trained in advance and must pass a test before they can begin recording the data. The data will then be analyzed using the Statistical Package for the Social Sciences (SPSS) software.

The data will be analyzed by an independent statistician. If the data are divided as measurement data, the mean, standard deviation (SD), minimum value, maximum value, and median will be used for comparison. Comparison among groups will be analyzed by analysis of variance (ANOVA) and pair-wise comparison, while heteroscedasticity data or abnormal distribution will be analyzed by the rank-sum test and pair-wise comparison. If the data are divided as count data, the constituent ratio and frequency will be used for comparison. Efficient comparison between groups will be analyzed by the chi-square test at an α = 0.05 given a 2-sided test.

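### The promised observer blinding cannot cover flatus timing or other interview-based data, because patients know their arm; for bowel sounds it is feasible, but the assessment windows allow avoidable unblinding

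*Protocol article*

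**What the plan says.** All references are to the protocol article.

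- **Quality control (2.8):** to keep the data objective, "we will ensure that the observers and statisticians were blinded". The section does not mention participants or treating staff.
- **Intervention (2.6):** the two arms are given as: "Yikou-Sizi powder hot compress and conventional therapy or only conventional therapy twice daily at 9:00 and 16:00 hours after surgery until the time to defecation". The control content is stated too: "Conventional therapy will only include antibiotics and liquid support". No sham or heat-only compress is described.
- **Trial procedure (2.5):** "The participants will be instructed to apply a Yikou-Sizi powder hot compress twice every day at 9:00 and 16:00 hours", from the day after surgery until defecation. Bowel sounds are checked at least three times a day, in the windows 1:00–9:00, 9:00–17:00 and 17:00–1:00.
- **Endpoints (2.9):** the primaries are "time to first flatus, time to first defecation, time to first bowel sounds, time to initiation of a liquid/semiliquid/general diet". Nausea, vomiting, abdominal distension and pain are secondary.
- **Data collection and statistical analysis methods (2.12):** data are "collected and recorded in the CRF forms from participants via face-to-face and telephone interviews daily".

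**The concern.** Blinding an observer protects an outcome only if the observer generates the information. When an unblinded patient supplies it, a masked interviewer merely writes it down. Here every patient knows whether a compress is being applied. Time to first flatus necessarily depends on what the patient notices and reports. Defecation times and symptoms are in the same position where they are taken from the daily interview. Patients who expect the compress to work may notice or report these events earlier, which would favour the compress arm.

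Bowel sounds differ because the observer makes the judgement and can be masked. The protocol does not, however, separate listening from treatment: a check may coincide with a compress or follow it closely.

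At stake is how a positive result would be read. As section 2.8 stands, a reader would take all four primaries as coming from blinded observation, and at least one of them cannot.

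**Working it through.** **Step 1. Which outcomes the blind can reach**

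| Outcome | Source of the information | Can a masked observer blind it? |
|---|---|---|
| First flatus (primary) | Patient's report | No |
| First defecation (primary) | Patient, where taken from the interview | Not where taken from the interview |
| Symptoms (secondary) | Patient, where taken from the interview | Not where taken from the interview |
| First bowel sounds (primary) | Auscultation | Yes, if nothing at the check reveals the arm |
| Start of diet (primary) | Not stated | Cannot be judged from the article |

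**Step 2. Compress times against auscultation windows (section 2.5)**

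- 1:00–9:00: the 9:00 compress lies on the closing boundary.
- 9:00–17:00: 9:00 lies on the opening boundary and 16:00 lies inside.
- 17:00–1:00: no compress time.

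A check in the middle window can therefore fall during or just after either session. A check just before 9:00, one just before 16:00 and one in the evening window would all comply with section 2.5 as written. The cue is permitted, not required.

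**Step 3. Illustration of size**

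Inputs from Sample size estimation (2.11):
- Flatus: means 75.47 and 64.29 h (difference 11.18 h), SDs 39.44 and 24.96.
- Bowel sounds: means 44.13 and 31.22 h (difference 12.91 h), SDs 32.58 and 24.26.
- Two-sided α 0.05, 80% power, 110 per arm within each surgery type.

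The plan's own figure first. With n = 2(1.96 + 0.84)²σ²/δ², the bowel-sounds difference and the simple average SD of 28.42 give 77 per group, as stated; the root-mean-square SD of 28.72 gives 78. The flatus inputs (root-mean-square SD 33.00) give 137, so 77 comes from the bowel-sounds figures. The present point does not rest on this.

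Standard error of the difference, SE = √[(S1² + S2²)/n]:
- Flatus: √[(39.44² + 24.96²)/110] = 4.45 h.
- Bowel sounds: √[(32.58² + 24.26²)/110] = 3.87 h.

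With no true effect and a mean shift b in favour of the compress, the chance of p < 0.05 is 1 − Φ(1.96 − b/SE) + Φ(−1.96 − b/SE).

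| Shift b (assumed) | Flatus | Bowel sounds |
|---|---|---|
| 0 h | 5.0% | 5.0% |
| 2 h | 7.3% | 8.1% |
| 4 h | 14.6% | 17.8% |

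At 77 per arm, shifts of 2 and 4 h give 6.6% and 11.7% for flatus, and 7.2% and 13.9% for bowel sounds.

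For scale, 2 h on bowel sounds means a quarter of compress patients credited one 8-hour window early (0.25 × 8 = 2) with no such shift in controls. For 4 h it is half of them (0.5 × 8 = 4). Against the planned differences, 4 h is 4/11.18 = 36% for flatus and 4/12.91 = 31% for bowel sounds.

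**The case against.** The strongest reply is that section 2.8 contains no contradiction. It names observers and statisticians only and never says that patients or ward staff are blinded. An open-label add-on trial with a masked assessor is a recognised design, and the logistics of masking may sit in a full protocol that is not shown. This stands in part: missing masking logistics are not the fault here. It does not answer the flatus endpoint, because no logistics can make a self-applied hot compress unknown to the patient.

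A reader might also infer more than the article supports:

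- **That no observer blind can be kept.** This is not shown. A masked auscultator is feasible, and checks away from the compress already fit the windows.
- **That odour or a visible abdominal dressing gives the arm away.** The Introduction says of the herbs, "They are all aromatic herbs to enliven and invigorate the spleen and resolve dampness", in describing their traditional action. The article gives no application site, duration or lingering smell.
- **That diet initiation is biased by unblinded ward staff.** The article does not say who decides or by what criterion, so demoting this primary on that ground is not warranted.
- **That the false-positive rate is known to be inflated by a given amount.** The shift is assumed. At 2 h the effect is small, and 4 h on bowel sounds needs half of the compress patients misdated by a full window. Pooling both surgery types would enlarge the figures, but the article states no pooled analysis.

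It is also fair to say that flatus timing remains patient-reported after any change of wording. The change corrects what is claimed for it and does not remove the bias.

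**Conclusion.** The point holds in this limited form. The blinding promise cannot extend to time to first flatus, nor to defecation and symptoms where these come from the daily interviews, because the design has no sham and patients apply the compress themselves. For bowel sounds the promise can be kept, but section 2.5 leaves open an avoidable cue. The statistician's blind is not in question.

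The size of any bias cannot be derived from the documents. The ranges of 7–15% for flatus and 8–18% for bowel sounds are illustrations. They rest on an assumed mean shift of 2 to 4 h, no true effect, the planning SDs, a normal approximation and 110 analysed per arm. They show that a shift well below the planned difference can matter. They do not show that one will occur.

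**What to change.** 1. **Restate the blinding in section 2.8.** Say that participants are not blinded, that the blind covers only the bowel-sounds observer and the statistician, and that the patient-reported primaries are open to expectation bias and will be interpreted as such.
2. **Fix the auscultation times in section 2.5.** Have the existing observer listen at set clock times within the three existing windows, before that session's compress and with none in place: for example just before 9:00, just before 16:00, and once in 17:00–1:00. Use the same times in both arms and ask patients not to reveal their arm. Optionally, record the observer's guess of the arm and report it.

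**Cost:** protocol wording and CRF instructions, a less favourable blinding statement, and slightly stricter assessment timing. The compress schedule and the endpoints stay as they are.
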